## Abstract

**Background:** This will be a before-and-after study nested within a randomized clinical trial. Its objective will be to analyze the effectiveness of a teleconsultation and validate a questionnaire for performing teletriage in dental urgency/emergency situations in children aged 3 to 13, whose parents will have signed a free and informed consent form, and who have had full access to the internet.

**Methods:** The Questionnaire for Teletriage of Emergencies and Urgencies in Pediatric Dentistry (QuesT-Odontoped)—will be validated by applying it to 140 randomized child parents/guardians. After validation, another 260 children seeking emergency dental care in the municipality of Carangola, Minas Gerais, Brazil, will receive a remote consultation, be randomized, and then allocated into two groups: G1, teleconsultation, and G2, teleconsultation and face-to-face consultation (immediately after the former) with a blinded evaluator, involving anamnesis and conventional clinical examination. The G2 sample will be used in the before-after study. Both groups will be followed-up for 7 and 14 days using pain and quality-of-life scales, applied at baseline and after each follow-up period. Clinical follow-up will be carried out after 12 and 24 months to assess the outcome of the tooth that had been indicated for treatment in the teletriage. The Mann-Whitney test will be used to assess pain; Student’s t test or the Mann-Whitney test will be used to assess quality of life and the number of missing teeth after 24 months; and Poisson’s regression analysis will be used to assess the influence of other variables. The significance level will be set at 5%.

**Conclusions:** In conclusion, this study expects to confirm the hypothesis that remote urgency consultation (teletriage), through a validated questionnaire, will be able to define the planning of the clinical situation, reducing the chance of displacements and progression of infection, helping to eliminate patient pain and discomfort.

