**Figure 3. f3:**
[figure not shown]
Inclusion of patients in the randomized control trial (before and after). G1, teleconsultation; G2, teleconsultation plus face-to-face consultation.

Patients in G1 and G2 will be followed up for seven and 14 days using specific instruments to assess the absence or presence of pain (Wong-Baker scale)
^
31
^ and quality of life, according to the child’s age (Child Perceptions Questionnaire, CPQ,
^
32
^ or Early Childhood Oral Health Impact Scale, ECOHIS).
^
33
^ In the case of urgencies involving teeth, a 12- and 24-month follow-up of the tooth reported in the teletriage will be carried out. The clinical criteria used to determine treatment success will be no fistula or exudate, no abscess, no painful symptoms, and no pathological mobility (
Figure 4).

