### Inclusion and exclusion criteria

The inclusion criteria will be the same for the two stages of patient selection in the study.

*Inclusion criteria*
a)children aged 3 to 13 years, with dental pain, whose parents seek urgent care at the Dental School of the University of São Paulo in São Paulo, or at the public network in the city of Carangola, in the state of Minas Gerais.b)patients with a sufficiently good internet connection to allow a synchronous consultation.

*Exclusion criteria*

The exclusion criteria will be the same for the two stages of patient selection of the study:
a)patients who fail to attend the face-to-face consultation, when assigned to G2;b)patients with internet access difficulties.

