Before-and-after studies are considered observational studies, and use a preliminary diagnostic test to decide whether or not to treat a series of examined patients. These patients are submitted to another diagnostic method, and the treatment decision can then be revised. Since this before-and-after study is nested within a randomized controlled trial (RCT), the sample size calculation will take into account the primary outcome of the RCT and the two experimental groups. However, only the group evaluated using both methods (teletriage + face-to-face consultation) will be eligible for this study. Therefore, the before-and-after study sample will consist of 130 patients.

*Outcomes*

Primary outcome: the presence of dental pain in children and adolescents, considering independent samples.

Secondary outcome: quality of life (questionnaires according to age group) and tooth loss.

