### Data analysis

*Questionnaire validation*

The kappa coefficient (k) and content validity index (CVI) will be used to quantify the degree of agreement among experts during content validation. In order to assess the reliability of the instrument, the test and retest results will be evaluated using the intra-examiner agreement test (kappa test,
*k*), which is the appropriate statistical procedure to assess the reliability of categorical and nominal variables. The criterion validity will be analyzed by comparing the results of the teleconsultation with those of the face-to-face consultation using the chi-square test (χ
^2^). The significance level will be set at 5%, and the data will be analyzed using
Jamovi and
RStudio software.

*Randomized clinical trial*

Primary outcome: pain (Wong-Baker scale); secondary outcomes: quality of life (questionnaires according to age group) and missing teeth.

The primary outcome of the randomized clinical study will be any change in pain score observed at the 7-day and 14-day follow-up timepoints compared to baseline. This outcome comprises an ordinal qualitative variable; therefore, comparison between the teleconsultation and face-to-face consultation groups will be performed using the Mann-Whitney test.

Other secondary outcomes will be evaluated, such as the impact of treatments on oral health-related quality of life, and the number of missing teeth after the 24-month follow-up period. Differences between the groups regarding the final and initial scores of the questionnaires on oral health-related quality of life, as well as the number of missing teeth, will be compared using Student’s t test or the Mann-Whitney test, depending on the type of data distribution (normal or non-normal). In addition, Poisson’s regression analysis will be performed to assess the influence of other variables on the results. The significance level will be set at 5%, and the data will be analyzed using Jamovi and RStudio software.

*Before-after study nested within an RCT*

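### The 24-month tooth-loss outcome is a count of missing teeth, but only the reported tooth is followed, and nothing separates normal shedding from other loss in children aged 3 to 13

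*Protocol article*

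**What the plan says.** Tooth loss is a secondary outcome, described in two ways in the protocol article. The Outcomes list under Sample size has "Secondary outcome: quality of life (questionnaires according to age group) and tooth loss". The Data analysis section for the randomized trial has "secondary outcomes: quality of life (questionnaires according to age group) and missing teeth", and then specifies the variable as "the number of missing teeth after the 24-month follow-up period". The analysis is a between-group test: the quality-of-life score differences, "as well as the number of missing teeth, will be compared using Student’s t test or the Mann-Whitney test", with the choice depending on the shape of the distribution. Poisson regression is added to examine other variables, which are not named.

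The long-term follow-up has a different unit. Research design says that, for urgencies involving teeth, "a 12- and 24-month follow-up of the tooth reported in the teletriage will be carried out". Table 1 repeats this, and the Abstract says the 12- and 24-month visits are "to assess the outcome of the tooth that had been indicated for treatment in the teletriage". Success at those visits means "no fistula or exudate, no abscess, no painful symptoms, and no pathological mobility". None of the four criteria says how to class a tooth that has been shed or extracted.

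The population is "children aged 3 to 13 years, with dental pain" at entry, so about 5 to 15 years old at the 24-month visit.

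**The concern.** The stated variable and the stated follow-up do not fit together. One followed tooth per child is present or absent at 24 months, which is a yes/no result. A number of missing teeth whose distribution decides between a t test and a Mann-Whitney test is a different variable, and it needs a wider examination than the one described. Two analysts could produce two different outcomes from the same text.

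The second difficulty is the age range. Between about 5 and 15 years, primary teeth are shed whatever care was given. As worded, the outcome counts such a tooth in the same way as one lost to infection, trauma or extraction. On a whole-mouth count, shedding adds a large component of variation unrelated to the intervention. On a single-tooth reading, the reported tooth may itself be a primary tooth that sheds within 24 months and is recorded as missing.

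The practical stake is interpretation. Research design labels the trial noninferiority, and the article states no margin for tooth loss. A diluted comparison that shows no difference could be misread as support for teleconsultation.

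**Working it through.** **Inputs.** The article gives no tooth-loss rate, shedding rate or power figure for this outcome, so there is no figure of the plan's own to reproduce; its sample size calculation concerns pain. From the article: 130 per group and a 10% dropout allowance, giving 130 × 0.90 = 117 per group; two-sided 5% level. Every rate and SD below is an assumption for illustration.

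**Reading 1: index tooth, missing or not.** Power is Φ[(d − 1.96·SE₀)/SE₁], where d = p₁ − p₂, SE₀ = √(2p̄(1−p̄)/n) and SE₁ = √[(p₁(1−p₁) + p₂(1−p₂))/n]. Let loss from causes other than shedding be 25% v 10%. If a fraction s of the otherwise surviving index teeth shed and count as missing, the observed proportions are 0.25 + 0.75s and 0.10 + 0.90s, so d = 0.15(1 − s).

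| s | observed | d | SE₀, SE₁ | power |
|---|---|---|---|---|
| 0 | 25% v 10% | 0.15 | 0.0497, 0.0487 | 86% |
| 0.20 | 40% v 28% | 0.12 | 0.0619, 0.0614 | 49% |
| 0.40 | 55% v 46% | 0.09 | 0.0654, 0.0651 | 28% |

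Here the risk difference itself shrinks, as well as becoming noisier.

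**Reading 2: whole-mouth count.** Suppose the same 15-point effect on one tooth, so the mean count differs by 0.15, and shedding gives a between-child SD σ. Then SE = σ√(2/117), and power with both tails is Φ(0.15/SE − 1.96) + Φ(−0.15/SE − 1.96).

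- σ = 1: SE = 0.131, power about 21%.
- σ = 2: SE = 0.261, power about 9%.
- σ = 3: SE = 0.392, power about 7%.

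For a larger difference of 0.40 teeth, power is about 33% at σ = 2 and 18% at σ = 3.

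**Simulation.** Poisson counts, 2000 runs per setting, 118 to 130 per group, t test. Heavy shedding assumes 20 primary teeth shed evenly from age 6 to 12 (24-month mean 3.6, SD 3.5). Light shedding assumes mean 1, SD 1.

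| loss other than shedding, teeth per child | no shedding | light | heavy |
|---|---|---|---|
| 0.50 v 0.25 | 88–92% | 36–40% | 9–10% |
| 0.60 v 0.20 | over 99% | 74–79% | 14–17% |
| 0.30 v 0.30 (no difference) | 5% | 5% | 5–6% |

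The Mann-Whitney results are similar. In the last row the rejection rate stays near the nominal 5%. On this reading shedding leaves the expected difference in mean counts unchanged and costs precision.

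**The case against.** A reader might infer that the trial counts every missing tooth in the mouth. The article does not say that. The analysis section gives no such qualifier, the Outcomes list says only tooth loss, no whole-mouth charting at 24 months is described, and the follow-up is confined to the reported tooth. The number of reported teeth that are missing is an available reading. This stands: the defect is an inconsistent unit, not an established whole-mouth count.

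A reader might also infer that the outcome cannot show an effect, or that a null result is almost certain. That is too strong. Allocation is random, so shedding is balanced in expectation and the test keeps its level. With light shedding and a larger effect, power is still 74% to 79%. The loss depends heavily on rates the article does not give. Setting 86% for a clean index-tooth outcome against 9% to 7% for a whole-mouth count is not a measure of what the plan's choice costs, since the index tooth can shed too.

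Poisson regression is planned and could include age. That could recover some precision, but the variables are unnamed, and no age adjustment can tell a shed tooth from one lost to infection.

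Finally, how to record cause of loss could be left to an analysis plan or case form, and its absence from an article would not be a finding by itself. Here, however, the article does state the variable, the time point and the tests, and they conflict with the follow-up it also states.

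**Conclusion.** The point holds as an inconsistency in a stated secondary outcome that is also poorly suited to this age range. On either reading, normal shedding would dilute or obscure a difference. On the index-tooth reading, an assumed 15-point difference shrinks to 12 or 9 points and power falls from about 86% to 49% or 28%. On the whole-mouth reading, power is about 9% to 7% for 0.15 teeth with SD 2 to 3, and higher with less shedding. That primary teeth shed in this age range is general knowledge; the rates and SDs are assumptions, so the figures show direction and plausible size only. The calculations use all 117 children per group, whereas the follow-up covers only urgencies involving teeth, so actual power would be lower.

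The type I error is not inflated and the primary pain outcome is untouched. The noninferiority misreading is a risk of interpretation; the article makes no such claim for tooth loss. This is a change that should be made because it is cheap and improves the outcome, not one on which the trial's main conclusion depends.

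**What to change.** Define the outcome as loss of the index tooth (the one reported in the teletriage) by 24 months for any cause other than normal exfoliation, among children whose urgency involved a tooth. Use the same definition in the Abstract, Outcomes and Data analysis sections.

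At the planned 12- and 24-month visits, record the reason for each loss (disease, trauma, extraction, normal shedding) and whether the tooth is primary or permanent. Do not count a normally shed tooth as lost.

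Compare the groups by a risk difference or risk ratio with 95% CI, adjusted for age and primary or permanent tooth. Keep any total count of missing teeth as descriptive, without a t test or Mann-Whitney test.

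The cost is one extra data field for the reason for loss at visits already planned, the revised wording, and a smaller analysis set, because children whose urgency did not involve a tooth drop out of this outcome. For example, at an assumed 90 per group, 25% v 10% gives SE₀ = 0.0566 and SE₁ = 0.0555, hence about 76% power. Study status says patients are still being included, so the reason can be collected prospectively; it would be hard to reconstruct later.

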### Confidentiality

The data collected will be stored using specific procedures to ensure the secrecy and confidentiality of the participants’ information. The access to the final trial dataset will be exclusive to the main researcher and the project supervisor. Only remote consultation platforms that have robust security standards, and that meet the regulations of the General Data Protection Law (LGPD) will be used to store the data. In addition, the research subjects will have the right to leave the study at any time, with no detriment to their care.

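### The quality-of-life comparison lets the observed distribution choose between means and ranks, and uses the baseline score only by subtraction, so the effect measure is not fixed and precision is lost

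*Protocol article*

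**What the plan says.** The Outcomes paragraph (under Sample size) gives quality of life a secondary role: "Secondary outcome: quality of life (questionnaires according to age group) and tooth loss".

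The Abstract describes "pain and quality-of-life scales, applied at baseline and after each follow-up period", so a baseline score is collected. The Research design section assesses "quality of life, according to the child’s age (Child Perceptions Questionnaire, CPQ" or, for the other age group, ECOHIS. Follow-up is at 7 and 14 days.

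The randomized clinical trial part of Data analysis sets the comparison: "Differences between the groups regarding the final and initial scores of the questionnaires on oral health-related quality of life". Tooth loss falls under the same sentence. The choice is between a t test and a rank test, and it is made "depending on the type of data distribution (normal or non-normal". The section names no default test, no criterion for normality and no effect measure. It does not say whether the final score is the one at day 7 or day 14.

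The only model named for the trial follows directly: "Poisson’s regression analysis will be performed to assess the influence of other variables on the results".

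**The concern.** Two features of this rule are weak.

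1. **The question is not fixed.** The t test addresses a difference in mean score. The Mann-Whitney test addresses whether a child in one group tends to rank above a child in the other. The two can differ in size and meaning, particularly for skewed, bounded integer scores. If a normality check selects between them, a reader cannot know before the data are in which quantity the trial will report.

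2. **The baseline score is underused.** A change score subtracts the whole baseline, whatever its correlation with follow-up. When that correlation is moderate, this carries baseline noise into the comparison. Using the baseline as a covariate lets the data set its weight.

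At stake are the interpretability and precision of a secondary outcome, not the validity of the trial.

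**Working it through.** The article gives no standard deviation, correlation, effect size or power for quality of life, so there is no planned figure to reproduce. The check has two parts.

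**Part 1: what the stated rule does.** The article names no normality criterion. The simulation assumed a Shapiro-Wilk test at 5% in each arm, then the t test if both arms pass and the Mann-Whitney test otherwise. It used no true difference, 4,000 runs per scenario and 118 per arm (half of the article's 236 before the dropout allowance). The distributions are assumptions.

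| Assumed change score | Sent to Mann-Whitney | Type I error of the two-step rule |
|---|---|---|
| Normal | 10% | 4.9% |
| Normal, rounded to integers | 16% | 5.0% |
| Skewed integer | 84% | 4.9% |

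The Monte Carlo standard error at 5% is √(0.05 × 0.95 / 4000) = 0.3 percentage points, so none of these error rates differs from 5%. The reported quantity does vary: even truly normal data switch to ranks about one time in ten, and skewed data stay with means about one time in six.

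**Part 2: precision.** Let s² be the score variance, equal at baseline and follow-up, and r the correlation between the two visits. Per child:

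- change score: 2(1 − r)s²
- follow-up adjusted for baseline: (1 − r²)s²
- ratio, adjusted to change: (1 − r²) / [2(1 − r)] = (1 + r)/2

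| r (assumed) | Change | Adjusted | Ratio | CI width ratio (square root) |
|---|---|---|---|---|
| 0.3 | 1.40 s² | 0.91 s² | 0.65 | 0.81 |
| 0.5 | 1.00 s² | 0.75 s² | 0.75 | 0.87 |
| 0.7 | 0.60 s² | 0.51 s² | 0.85 | 0.92 |

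Inverted, the change score has 1.54, 1.33 and 1.18 times the adjusted variance. The sample size cancels, so the ratio applies within each instrument whatever the age split.

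The direction does not need equal variances. With standard deviations s₀ at baseline and s₁ at follow-up, the change-score variance minus the adjusted variance is (s₀² + s₁² − 2r s₀s₁) − s₁²(1 − r²) = (s₀ − r s₁)², which is never negative. The cost of estimating one slope is ignored.

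**Alternative reading.** If the sentence means comparing final scores alone, the variance is s² and the adjusted analysis has 1 − r² of it: 0.91, 0.75 and 0.51 for the same correlations. Neither reading uses the baseline as a covariate.

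**The case against.** In favour of the plan, the following can fairly be said.

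- **A change-score comparison is valid in a randomised trial and does use the baseline.** This is correct. The baseline enters by subtraction, so the point is efficiency and not bias.
- **The gain is modest if the correlation is high.** This also stands: at r = 0.7 the variance falls by 15%, against 35% at r = 0.3.
- **The regression for other variables could include the baseline score.** It could, but the article does not name that score there, and the regression does not replace the group comparison by t test or Mann-Whitney test.
- **Covariates are often left to an analysis plan.** That is so, but the data-dependent choice of test is a rule the article itself states.

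Three stronger readings are tempting and are not supported.

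- A reader might infer that the rule inflates type I error, or that the analyst may take the smaller of two p-values. The article ties the choice to the distribution and not to the results, and under that rule the error rate stays near 5%.
- A reader might infer that someone who knows the allocation chooses the test. The Ethics statement has the main researcher assign participants, and Confidentiality says "The access to the final trial dataset will be exclusive to the main researcher and the project supervisor". Neither passage says who selects the test or whether that person works with the groups unmasked.
- A reader might dismiss normality on the strength of 130 children per group, or restate the loss as a number of children per group. CPQ and ECOHIS are used by age, so an analysis by instrument has fewer than 130 per group, and the article does not give the split.

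**Conclusion.** The point holds in this limited form. The stated rule leaves the quality-of-life effect measure to be settled by the data, and it does not use the baseline score as a covariate. Against a change-score comparison, baseline adjustment would need 65%, 75% or 85% of the variance at correlations of 0.3, 0.5 or 0.7. These correlations, and equal variances at the two visits, are assumptions. The direction holds for every r below 1 under equal variances.

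The error rate is not affected, and quality of life is secondary. The change is worth making because it costs almost nothing and gives one interpretable estimate.

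**What to change.** In Data analysis, replace the distribution-dependent choice for quality of life with one analysis named in advance:

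- a linear model of the follow-up score on group and baseline score, whatever the distribution;
- fitted separately for CPQ and ECOHIS, or on scores standardised within instrument if one combined estimate is wanted;
- robust or bootstrap standard errors;
- the adjusted mean difference with 95% CI as the reported result;
- a named final timepoint, for example day 14;
- the Mann-Whitney test as a sensitivity analysis only.

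The same sentence also governs the number of missing teeth. That outcome needs its own wording, since a linear model with a baseline score is proposed here only for quality of life.

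The cost is a change of wording. The baseline scores are already collected, and no visit, instrument or child is added. Study status reports that patients are still being included, so the text can be settled before the outcome data are complete.
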